**Setting::**

The primary outcome for evaluation is an 18% reduction in hypertriglyceridemia (≥150 mg/dL) between pre and postintervention measurements. Baseline characteristics of the study population will be summarized separately within each randomized group, and will use tests for continuous and categorical variables. For all tests, a *P* < .05 will be considered significant. The analysis of primary and secondary outcomes will use an intention-to-treat population and a per-protocol population. The primary and secondary outcomes will be compared separately between each treatment group and placebo, using binary logistic regression or regressão de Poisson for proportions (for binary outcomes) and using linear regression for differences in means (for continuous endpoints), with 95% confidence intervals.

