### Outcome measures

2.4

The primary outcome to be evaluated is an 18% reduction in hypertriglyceridemia (≥150 mg/dL) between the pre and postintervention measurements. The secondary outcomes to be evaluated are a 36% reduction in hypertriglyceridemia (≥150 mg/dL) between the pre and postintervention measurements with 28,000 IU of vitamin D; an 18% reduction in high LDL cholesterol (≥130 mg/dL) between the pre and postintervention measurements; an 18% reduction in waist circumference (≥90 cm men; ≥80 cm women) between the pre and postintervention measurements; and a reduction in low cognitive impairment (by cognition tests) between the pre and postintervention measurements.

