### Sample size

2.6

The sample was calculated with the following assumptions: the percentage of hypertriglyceridemia in the group not exposed to vitamin D replacement (40%)^[23]^; the percentage of hypertriglyceridemia in the group exposed to vitamin D replacement (22%)^[11]^; and the likelihood ratio equal to 2.3^[11]^, considering 80% power and a 95% confidence level. As a result, this study requires 106 participants in each group; after adding 10% for losses, a total of 350 participants at least were enrolled. To estimate the sample size, OpenEpi software (Open Source Epidemiologic Statistics for Public Health, EUA) version 3.01, a web-based epidemiologic and statistical calculator for public health, was used.

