The analysis of primary and secondary outcomes will use an intention-to-treat (ITT) population and a per-protocol (PP) population. ITT population includes all participants for whom outcome data are available, in the group to which they were randomized, regardless of the treatment actually received. PP population excludes individuals who did not comply with the protocol. The primary and secondary outcomes, which are hypertriglyceridemia, high LDL cholesterol, waist circumference, and low cognitive impairment, will be compared separately between each treatment group and placebo, using binary logistic regression or regressão de Poisson, if the outcome is rare, 5% or less, and the relative risk (RR) is less than about 2^[47]^ for proportions (for binary outcomes), and using linear regression for differences in means (for continuous endpoints), with 95% confidence interval (CI). An analysis will be performed to check whether adjusting for age, duration of shift work, physical activity level, alcohol consumption, lower cholesterol drugs, and foods consumption (fiber, total carbohydrates, total fat, and saturated fat) has any impact on the estimated treatment effects; if it has no impact, then they will not be included in the model. Statistical analyses will be calculated using PASW (Predictive Analytics Software, SPSS Inc, Chicago, IL) version 17.0 and R software (R Development Core Team) version 3.5.1.

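### The rare-outcome condition is attached to Poisson instead of logistic regression, so as printed the common primary outcome is estimated as an odds ratio, off the scale of the stated hypothesis

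*Protocol article*

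**What the plan says.** Section 3.2 (Statistical methods) offers two models for the binary outcomes: "using binary logistic regression or regressão de Poisson, if the outcome is rare, 5% or less, and the relative risk (RR) is less than" (the bound given is about 2). The condition comes straight after Poisson, and no separate condition is given for logistic regression. The abstract, under Setting, has only "using binary logistic regression or regressão de Poisson for proportions (for binary outcomes"), with no condition, so it does not settle which model applies when.

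The effect is stated as a change in a proportion. Section 2.4 (Outcome measures) says: "The primary outcome to be evaluated is an 18% reduction in hypertriglyceridemia (≥150 mg/dL"). The hypothesis at the end of the Introduction uses the same 18%. Section 2.6 (Sample size) plans on 40% hypertriglyceridemia without vitamin D and 22% with it, which is 18 percentage points. The same section also lists "the likelihood ratio equal to 2.3".

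**The concern.** A rare outcome with a modest relative risk is the setting in which the odds ratio from a logistic model can stand in for a risk ratio. A model that estimates the risk ratio directly is useful in the opposite setting, where the outcome is common. The printed rule keeps Poisson for outcomes of 5% or less and leaves logistic regression for everything else, including a primary outcome planned at 40%.

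What is at stake is the scale of the headline estimate. The trial's hypothesis is about how many fewer participants have hypertriglyceridemia. Followed literally, the rule yields an odds ratio where that measure differs clearly from the risk ratio, and the article names no step that converts it back to risks. A statistician who suspects the sentence was reversed cannot tell from the text which model was intended for the primary analysis.

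**Working it through.** **Inputs.** Section 2.6: 40% without and 22% with vitamin D, 80% power, 95% confidence level, 106 per group, 10% for losses, total 350. Section 2.1: allocation 1:1:1. A two-sided test is my assumption; the article does not state it.

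**The plan's own figure.** Two proportions, no continuity correction, mean proportion 0.31:
- n = [1.96 × √(2 × 0.31 × 0.69) + 0.8416 × √(0.40 × 0.60 + 0.22 × 0.78)]² / 0.18² = 102.4, so 103 per group.
- With the pooled variance in both terms: (1.96 + 0.8416)² × 2 × 0.31 × 0.69 / 0.18² = 103.6, so 104.
- Both are within 3% of the stated 106. Total: 3 × 106 = 318, and 318 × 1.10 = 349.8, so 350.

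The planning rates are therefore a fair basis for what follows.

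**Which model the rule selects.** 40% and 22% are both far above 5%. The Poisson condition is not met, and logistic regression remains.

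**Effect measures at the planning rates.**
- Risk difference: 0.40 − 0.22 = 0.18.
- Risk ratio: 0.22 / 0.40 = 0.55, a 45% lower risk (inverse 1.82).
- Odds ratio: (0.22/0.78) / (0.40/0.60) = 0.423, 58% lower odds (inverse 2.36).

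**The same risk ratio where the outcome is rare.** Control rate 5%, treated rate 0.05 × 0.55 = 0.0275. Odds ratio: (0.0275/0.9725) / (0.05/0.95) = 0.537, against a risk ratio of 0.55. The two nearly agree, so rarity is the condition that would excuse a logistic model.

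**If the 18% were a relative reduction.** With a risk ratio of 0.82, the odds ratio is 0.732 at a 40% control rate and 0.812 at 5%. The gap is smaller but follows the same pattern.

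**If the reverse rule was meant** (logistic when rare, Poisson otherwise). With 106 per group, expected events are 106 × 0.40 = 42.4 and 106 × 0.22 = 23.3.
- Model-based Poisson SE of log RR: √(1/42.4 + 1/23.3) = 0.258.
- Binomial SE, which a robust variance approximates: √(0.60/42.4 + 0.78/23.3) = 0.218.
- Ratio: 0.258 / 0.218 = 1.18, so the interval on the log scale would be about 18% too wide.

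**The case against.** The strongest reply is that this is a wording slip. The sentence is loosely punctuated, the condition may have been meant for logistic regression, and the term odds ratio is never used for the result. An odds ratio is in any case a legitimate measure, and the test of no effect does not suffer because it differs from the risk ratio. Nor is an odds-type ratio foreign to the planning: the listed 2.3 is close to the odds ratio of the two rates (2.36) and not to their risk ratio (1.82). If 2.3 is applied as an odds ratio to 40%, the treated rate is 22.5% and the sample size 109 per group, so the stated 106 lies between the two routes.

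Most of this stands as a limit on the point. None of it repairs the sentence. The printed order attaches the condition to Poisson, and even a slip leaves the primary model unclear. The outcome and hypothesis are worded as reductions in hypertriglyceridemia, whatever ratio entered the sample-size software.

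Some stronger readings are tempting but not supported:
- **That the effect will be reported misleadingly.** Nothing says that an odds ratio will be presented as a risk reduction.
- **That the plan loses power through Poisson standard errors.** This needs both the reverse reading and a model-based variance. The article does not name a variance estimator, and that detail may sit in a fuller document. On the literal reading, Poisson is not used for the primary outcome at all.
- **That the model is picked from the trial's own result.** The text does not say that the relative risk and prevalence are the observed ones, and at the planning rates the choice is settled beforehand.
- **That the 28,000 IU comparison would switch model because 40% less 36 is 4%.** This takes the 36% in section 2.4 as percentage points; a relative reading gives 0.40 × 0.64 = 25.6%. It also judges rarity in one arm, whereas 40% and 4% average 22% across the comparison.

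**Conclusion.** The rule is wrong as written. It assigns the rare-outcome condition to Poisson and so sends a primary outcome planned at 40% against 22% to logistic regression. There the odds ratio is 0.42 and the risk ratio 0.55: 58% lower odds against 45% lower risk, for a planned difference of 18 points. The consequence is a mismatch of scale, with overstatement if the estimate is read as a risk reduction. Type I error, the validity of the test and the sample size are not in question.

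This rests on the plain reading of the sentence and on the planning rates. The trial's own rates may differ, since entry requires at least one altered risk factor, but on the article's figures a rate of 5% or less for hypertriglyceridemia is implausible. If the authors meant the reverse, the sentence still has to be corrected, and the variance method then matters at the 18% level shown above.

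**What to change.** In section 3.2, delete the condition on 5% and a relative risk below about 2, and name one approach for the binary endpoints. Either of these would serve:
- Poisson regression with a log link and robust (sandwich) variance, with the risk difference taken from the standardised risks of the same model.
- Logistic regression standardised to marginal risks in each arm.

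In both cases report the risk ratio and the risk difference with 95% confidence intervals for each dose against placebo. An odds ratio may be shown as well, labelled as such. Bring the abstract into line.

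If the authors prefer to keep two models, the least repair is to state that logistic regression applies to rare outcomes and Poisson to the others, and to name robust variance for Poisson.

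The cost is one sentence plus the matching phrase in the abstract. Both approaches run in R, which the section already names, and nothing changes in the sample size, visits or data collected. The article says the trial is still running, so the change should be recorded before the allocation code is opened.

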### Randomization

2.8

Randomization will be used to ensure a balance between the 2 intervention groups and placebo group for deficient and insufficient vitamin D frequencies. The groups were also balanced by the following cardiovascular risk factors: fasting glucose, HDL cholesterol, triglycerides, LDL cholesterol, blood pressure, and waist circumference (Table 1).

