Seventh step: The subsample metrics are compared. The sample whose subgroup division presents the lowest value of *D* is maintained as the most probable sample to the original and will be the basis of the next simulation. The sample with the highest value of *D* will be discarded.

Eighth step: Repeat 6th–7th steps until the metric *D* reaches a predetermined stopping criterion or until a certain maximum number of simulations occurs. The sample with the lowest *D* value will be the one with the highest similarity in terms of the proportion of the categorical variables between the groups when compared to the original proportions.^[24]^

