### Data collection

3.1

The screening was performed in a population of 686 rotating shift workers; all individuals were invited to a general health assessment. All data were collected at the company's clinic through face-to-face interviews with a structured questionnaire assessment and a blood draw. The team responsible was composed of nurses, biochemists, nutritionists, and students, who were trained to collect the data before the study.

Figure 1 demonstrates all measurements that were evaluated at the screening visit, follow-up visits, and at the end of the 12-month supplementation period. At the screening visit, we are evaluating socioeconomic status, pre-existing diseases, drug use, sun exposure, lifestyle profile, quality of life, cognition (Table 2), blood pressure, biochemical data (Table 3), and anthropometrics and body composition measurements (Table 4). The follow-up visits will occur every 4 months and the supplementation delivery will occur every 2 months (it was integrated with follow-up visits). The follow-up visit procedures include blood sample collection, waist circumference measurement, and questionnaire interview. The vitamin D and lipid profile levels were quantified. The follow-up questionnaire monitors a presence of vitamin D intoxication, disease symptoms, drugs use, vitamins and minerals supplements, disease presence, treatment and others interventions during the trial, and food consumption alteration. At the end of the 12-month supplementation period, a reassessment of the general state of health was performed (Fig. 1).

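### The primary model is left to a keep-or-drop rule with no threshold, and its covariate list omits baseline triglycerides and every factor that the allocation balanced

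*Protocol article*

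**What the plan says.** Section 3.2 (Statistical methods) of the protocol article compares each dose with placebo, by logistic or Poisson regression for binary outcomes and by linear regression for continuous ones. It then plans a check on "adjusting for age, duration of shift work, physical activity level, alcohol consumption, lower cholesterol drugs, and foods consumption", with four dietary items named. The test is whether adjustment alters the estimated effect at all: "if it has no impact, then they will not be included in the model". The article does not say how large an impact counts or on which scale it is judged. It also does not say which model is primary if the two disagree. Baseline triglycerides appear in the section only as a characteristic to be summarised by group.

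Section 2.8 (Randomization) aims at "balance between the 2 intervention groups and placebo group for deficient and insufficient vitamin D frequencies", and adds: "The groups were also balanced by the following cardiovascular risk factors: fasting glucose, HDL cholesterol, triglycerides, LDL cholesterol, blood pressure, and waist circumference". The algorithm draws random splits of the eligible sample and compares them on a distance *D*. Its seventh step reads "The sample whose subgroup division presents the lowest value of" *D* is retained. This is constrained randomisation on seven factors. None of the seven is in the adjustment list of section 3.2.

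**The concern.** There are two linked problems.

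- **The model is chosen after the effect has been seen.** Without a threshold, two analysts could report different primary estimates from the same data and both claim to follow the plan. The criterion is also weak for a logistic model. The odds ratio is non-collapsible, so adjusting for a prognostic covariate moves it away from 1 even under perfect balance. A change in the odds ratio is therefore no sign of confounding.
- **The analysis ignores the design.** When allocation forces balance on factors related to the outcome, the effect estimate varies less between trials than an unadjusted model assumes. The unadjusted standard error is then too large, and the test is conservative and loses power. Triglycerides of at least 150 mg/dL are only one of six qualifying criteria (section 2.2), so the sample can mix people above and below the outcome cut-off at entry. Baseline triglycerides are then the obvious predictor of the primary outcome.

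**Working it through.** **1. The plan's own figure.** Section 2.6 gives 40% against 22%, 80% power and 95% confidence.

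- Fleiss: n = [1.96·√(2·0.31·0.69) + 0.842·√(0.40·0.60 + 0.22·0.78)]² / 0.18² = (1.282 + 0.540)² / 0.0324 ≈ 102.5, so 103 per group. Kelsey gives 104.
- The stated 106 is within 3% of both, and its power is 0.813.
- 3 × 106 = 318, and 318 × 1.10 = 350, as stated.

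The sample size reproduces and this point does not affect it.

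**2. Simulation set-up.**

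- From the article: 40% and 22%; 1:1:1 allocation; 362 enrolled (section 4.1), so about 120 per arm before losses; seven balancing factors; the split with the smallest distance is kept.
- Assumed: pre-post triglyceride correlation 0.5 or 0.7; each factor binary with 40% prevalence (the Table 1 categories are not visible); best of 200 random splits; nine weakly prognostic listed covariates, independent of treatment.
- 2000 trials per setting, one dose against placebo, logistic regression, Wald test on the log odds ratio. The risk difference (RD) is standardised over the sample. The adjusted model has continuous baseline triglycerides plus the other six factors.

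**3. Unadjusted analysis, no true effect.** By hand, the usual standard error (SE) of the RD is √(2·0.40·0.60/120) = 0.0632. The simulated model SE is 0.0630.

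| Correlation | Model SE | True SE | Ratio | Rejection of a true null |
|---|---|---|---|---|
| 0.5 | 0.0630 | 0.0615 | 1.02 | 4.3% |
| 0.7 | 0.0630 | 0.0559 | 1.13 | 2.8% |

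As a check, a ratio of 1.127 moves the effective cut-off to 1.96 × 1.127 = 2.21, a two-sided 2.7%. With the planned effect the ratio is about 1.06 at both correlations (0.0583/0.0549 and 0.0584/0.0552). The listed covariates do not repair this at 0.7: model SE 0.0612, true SE 0.0553, rejection 2.4%.

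**4. Baseline triglycerides and the other factors added.**

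| Correlation | Power, unadjusted | Power, adjusted | Rejection of a true null, adjusted |
|---|---|---|---|
| 0.5 | 0.88 | 0.92 | 5.6% |
| 0.7 | 0.87 | 0.95 | 4.5% |

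The null model SE of the RD falls from 0.063 to 0.057 (0.5) or 0.051 (0.7).

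**5. The selection rule.** Impact is read here as a 10% change in the log odds ratio (assumed).

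- The adjusted model is chosen in 80% to 82% of null trials and in 50% to 53% of trials with an effect.
- Null rejection under the rule is 5.5% (0.5) and 2.9% (0.7). Free choice of the more significant model gives 6.1% and 3.3%. The Monte Carlo error is √(0.05·0.95/2000) ≈ 0.5 points.

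**6. Impact without confounding.** In the trials with an effect, the listed covariates are unrelated to treatment by construction. Adding them still moves the mean log odds ratio from −0.876 to −0.965 (0.5) and from −0.863 to −0.958 (0.7), about 10% to 11%. The mean RD stays at about −0.18 throughout.

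**The case against.** - **The rule does little damage to the error rate.** This stands. A reader might infer that effect-driven selection invalidates the nominal 5% and 95% levels. Under the 10% reading, null rejection is 5.5% and 2.9%, against 5.6% and 4.5% for the recommended model, which is no clear excess given the Monte Carlo error. The rule also reads most naturally as one choice between two models, with the whole set in or out. The defect is that the reported estimate is not fixed.
- **The unadjusted analysis is conservative and still exceeds 80% power.** This stands too. The loss is of efficiency and calibration, not validity.
- **The intervals are not too wide on the odds ratio scale.** Correct. At 0.7 under the null, the log odds ratio SE rises from 0.265 unadjusted to 0.333 adjusted. The excess width holds only against true variability under this allocation, or on the risk-difference or mean scale.
- **The primary outcome is worded as a pre-to-post change (section 2.4), which may bring baseline in.** It might, but the article defines no change variable or model that does so.
- **Post-randomisation adjustment.** A reader might infer that lipid-drug use or diet recorded during follow-up will enter the model, since section 3.1 says: "The follow-up questionnaire monitors a presence of vitamin D intoxication, disease symptoms, drugs use, vitamins and minerals supplements". The article does not say so. Drug use and lifestyle are recorded at screening, and section 3.2 lists age, alcohol, activity and diet as baseline characteristics. Baseline values are a natural reading.
- **These are details for an analysis plan.** A fuller plan could settle them, but the keep-or-drop rule and the covariate list are written in the article and would have to be overridden.

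**Conclusion.** The point holds as a should-fix. The primary model is not fixed in advance, the criterion for choosing it is unsuited to the odds ratio, and the covariate list ignores the balance built in by the allocation.

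The size depends on a pre-post triglyceride correlation that the article does not give, and on the assumed number of splits and binary factors. Over 0.5 to 0.7 at 120 per arm, true type I error is about 4.3% to 2.8%, the null SE of the risk difference is about 2% to 13% too large, and adjustment adds about 4 to 8 points of power. Losses to follow-up were not simulated. The documents do not support calling the planned test invalid or the trial underpowered.

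The odds ratio argument applies to the logistic model. Under the Poisson alternative the risk ratio lacks this defect, but the missing threshold and the omitted factors remain.

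**What to change.** - Delete the rule that drops covariates without impact.
- Prespecify one primary model: treatment, baseline log triglycerides and the Table 1 balancing factors, all at screening values, kept whatever they do to the estimate.
- Report a standardised risk difference beside the odds ratio. Use a bootstrap or robust variance: in the simulation the model-based SE of the adjusted risk difference was somewhat small (0.0571 against a true 0.0598 at 0.5 under the null; 0.0477 against 0.0511 at 0.7 with the effect).
- Make the other listed covariates, at baseline values, a sensitivity analysis.

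The cost is wording only, because the balancing factors had to be known before allocation. The small downside is that the adjusted odds ratio is conditional and its interval is no narrower. At the planned rates one dose comparison has about 120 × (0.40 + 0.22) = 74 events. That is about nine per term for eight terms (treatment, log triglycerides and six other binary factors), so factors with several categories should be coded sparingly.

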### Trial monitoring

3.3

This trial will be monitored by a data monitoring committee (DMC), Trial Steering Committee (TSC). That includes biostatistics, epidemiologist, cardiologist, occupational physician, nutritionist, and internal member of the company. The TSC performs the following indicators of the work execution, through reports and seminars. The DMC will perform the monitoring during and at the end of the study for endpoints settings and code opening. Interim analysis is performed to assess the sample losses after each follow-up visit.

